### Verbal learning and memory test

To assess verbal memory, the “verbaler Lern- und Merkfähigkeitstest” (VLMT) [20], a modified German version of the Rey Auditory Verbal Learning Test [21] will be administered. This test can be used to evaluate short-term memory, learning, episodic memory and verbal discriminability. First, a list of 15 words is read to the patient by the investigator. The direct retrieval by the patient is scored as short-term memory performance. Second, the patient has to learn the word list in five learning trials. The sum of the recalled words represents a learning parameter. Third, a second word list with new words is presented verbally, and recalled only once for interference. After this, the learned words on the first word list have to be recalled. This is used as a measurement of a short-delayed function of verbal episodic memory. A second verbal episodic memory measurement is performed 20 min later (long delay). Finally, the verbal recognition ability is assessed by discriminating between already learned and new words. Between the short-delayed verbal episodic memory trial and the long-delayed verbal episodic memory trial, nonverbal cognitive tests are performed to avoid the potential effect of interfering words not included in the learned wordlist. Three parallel versions of this test are available and are implemented during baseline and follow-ups in alternating order.

### Rey-Osterrieth Complex Figure Test

In the Rey-Osterrieth Complex Figure Test (ROCFT) [22], the subject is first asked to copy a complex figure (visuo-construction/action planning). After about 30 min, the subject is then asked to draw the figure again from memory (visual memory).

### Trail Making Test

Selective attention and cognitive flexibility are examined using the Trail Making Test (TMT) [23]. It consists of subtests A and B. In TMT-A, the patient has to link numbers in ascending order as quickly as possible with a pencil (visual scanning and basal psychomotor speed, selective attention) on a test sheet. TMT-B additionally requires the ability of cognitive flexibility by switching between letters and numbers. The quotient formed from the processing time of subtest B and subtest A (B/A) can be used to represent a measure of cognitive switching ability (serial cognitive flexibility, executive function) independently of any psychomotor slowing.

### Wechsler Memory Scale (subtest digit span)

The subject is instructed to repeat successively increasing sequences of numbers forward (memory span, attention) and backward (working memory, executive function) on the "digit span" subtest of the Wechsler Memory Scale—Revised (WMS-R) [24].

### Regensburg-word-fluency-test

Semantic and phonemic verbal fluency will be tested using the “Regensburger Wortflüssigkeitstest” (RWT) [25] which also exists in parallel versions. In this test, the patient is asked to name as many words as possible that belong to a specific category (e.g. animals) within 1 min. For the phonemic word fluency subtest, the target is to name as many words as possible within 1 min that begin with a specific letter. This is a test for divergent thinking (executive function).

### Possible stress-related mediators and moderators

#### Anxiety and depression

The HADS-D [26] the German version of the Hospital Anxiety and Depression Scale by Zigmond and Snaith will be administered [27]. It is a standardized self-report screening instrument with two scales that capture anxiety and depression. Each scale is represented by seven items presented alternately. Each item is scored on a four-point Likert scale. The questions measure the expression of anxious and depressive symptoms referring to the last week. The items of the anxiety scale mainly refer to symptoms such as worry, apprehension, nervousness, and motor tension. The items of the depression scale focus on loss of motivation and interest, reduction of joy, and reduced drive. The questionnaire is well suited for recording reactive disorders in the physically ill. Another advantage is the quick completion time of approximately five minutes.

#### Self-assessment of cognitive failure

Study individuals will complete a validated German version of the Cognitive Failure Questionnaire for self-assessment (s-CFQ) [28]. It represents a procedure for self-assessment of the frequency of committed everyday errors, in the areas of perception, memory, and action regulation (executive functions). The CFQ has been used, revised, extended, and validated in numerous studies [28, 29].

### Stress experience

The Perceived Stress Scale [30] is used to assess subjective stress levels. With 10 items on a scale from “never” (0) to “very often” (4), the scale measures the occurrence of stress (feelings of being overtaxed, loss of control) in the last month. The German translation showed good internal consistency and construct validity [31].

We extended this questionnaire to include stress levels before and after testing prior to planned transplantation by the item “How stressed do you feel at the moment?” (1–10).

This allows us to measure the acute stress level at the beginning and at the end of the cognitive test and thus to investigate the difference in stress levels between the groups as well as the influence of the current stress level on cognitive functions.

### Hair cortisol

A hair sample is taken from the included individuals at each measurement time point for the determination of hair cortisol. Two to three thin hair strands are cut as close to the scalp as possible at the position of the posterior vertex. This protocol has been used successfully in studies for over 10 years and is well accepted by study participants [32]. The strands are first preserved and then sent to the laboratory of the Clinical Psychology of Adulthood at the University of Vienna ([name]. [name]) for hair cortisol analysis. For the determination of cortisol, commercial immunoassays with chemiluminescent detection (CLIA) from IBL, Hamburg, Germany, are used. For hair cortisol, high test–retest reliability as well as positive correlations with cortisol values from other media (e.g., saliva and urine), and with subjective stress measures are shown [33]. Hair cortisol levels of the first three centimeters from the scalp can be considered a measure of cumulative HPA axis activity over the previous three months [34].

In order to check the influence of steroids on the HPA axis, steroid doses are documented in all patients. Patients do not receive cortisone until transplantation. During transplantation, patients receive a cortisone shot of 1 g prednisolone on the day of transplantation. At the time of discharge from the hospital, the maintenance dose is 10 mg. The dose is usually reduced by 2.5 mg every 3 months and patients are no longer administered cortisone after 12 months. Furthermore, unscheduled intake of cortisone (e.g., during rejection episodes) is documented.

### Patient baseline data, comorbidity, laboratory parameters

In addition, baseline patient data, such as age, type of underlying disease, type and duration as well as the dose (*Kt/V*) of the dialysis therapy will be obtained. Comorbidities, that may have an impact on cognitive performance (such as previous stroke, coronary heart disease, hypertension diabetes mellitus, existing dementia or depression), will be documented. Furthermore, blood parameters such as hemoglobin, creatinine, calcium, phosphorus, albumin, triglycerides, cholesterine, urea, pH-value, CO_2_, and bicarbonate will be recorded. Current medication data will be obtained from the medical records and by self-report at each testing session. In addition, changes in medication are recorded. The examinations,were executed by trained and certified medical students.

### Statistical analysis

This is a within-group design with three measurement time points. We will investigate the proportion (percentage) of individuals that fulfill the above mentioned criteria at each given time point as estimates of prevalence of MCI and major neurocognitive impairment. Furthermore, we will conduct repeated-measures analysis of variance to investigate changes in cognitive performance over time, as well as the influence of different predictors. Cognitive performance of the individuals as a composite score and for each cognitive domain constitutes the dependent variables. The time of measurement and other control variables listed above represent the independent variables. A possible accumulation of the type I error is counteracted by an *α*-error correction (see below). The partial Eta-squared is calculated as the effect size, and the pairwise post-hoc comparisons are also corrected for multiple comparisons. The requirement of normal distribution is evaluated by the Kolmogorov–Smirnov test. Variance homogeneity is checked by Levene’s test. If the prerequisites for parametric statistics are not fulfilled, a distribution assumption-free covariance analysis according to the Quade model with rank-transformed variables is performed as an alternative.

Further questions are evaluated in terms of exploratory data analysis. Group differences are assessed using the t-test for independent samples or the Mann–Whitney-*U* test, depending on the scale level. Panels with discrete characteristics are analyzed with the *χ*^2^-test. Measures of correlation for discrete variables represent the contingency coefficients. For continuous characteristics, correlation measures according to Pearson (product-moment correlation) or Spearman (rank correlation) are used depending on the data level, in exceptional cases also according to Kendall (rank correlation without equidistance assumption).

The global significance level is set at *α* = 0.05. A false discovery rate (FDR) is calculated for *α*-error correction in multiple comparisons [35]. In the stepwise procedure, p-values are ranked in descending order; the null hypothesis is rejected if:1$$p(i) \le \frac{i}{m}\alpha$$ where *m* represents the number of *p* values and *i* the rank of the *p* value. Assuming *i* = 1, the FDR is equivalent to the Bonferroni correction.

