**Methods:**

We are conducting a prospective single-center cohort study involving 100 kidney transplant individuals. Individuals who are wait-listed to receive a kidney transplantation or have already received one will be included in this study. Individuals will undergo a battery of detailed neurocognitive tests at baseline (in part before surgery), and then 3 and 12 months afterwards. Furthermore, the enrolled patients will complete a validated German version of the Cognitive Failure Questionnaire for self-assessment (s-CFQ) as well as the Hospital Anxiety and Depression Scale -Deutsche (HADS-D), a self-report screening instrument with two scales that capture anxiety and depression. In addition, a hair sample will be taken at each measurement time point for the determination of hair cortisol levels as a parameter for the cumulative hypothalamic-pituitary-adrenocortical axis activity over the previous three months. The primary outcome measure will be (a) the effect of kidney transplantation on the cognitive performance up to 12 months after transplantation and (b) the course of cognitive performance following kidney transplantation over time.

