### Inclusion and exclusion criteria

Individuals who are scheduled to receive a kidney transplantation (immediate—deceased kidney donor, or within the following 2 weeks—living kidney donors) or have already received a kidney transplantation in the past will be included in this study. Due to the use of a standardized psychological assessment, individuals have to be native German speakers and at least 18 years of age. individuals under the legal supervision of a caregiver and with preexisting psychiatric disorders will be excluded from the study.

The study is divided into two parts (Table 1).

**Table 1 Tab1:** Trial schedule of enrollment and assessments

		Enrollment		Post-allocation	
Study Period, Part A					
Time point		*t*_−1_	*t*_1_	*t*_2_	*t*_3_
Enrollment					
Eligibility screen		X			
Informed consent		X			
Allocation		X			
Interventions					
Kidney transplantation			X		
Assessments					
ROCFT		X		X	X
VLMT		X		X	X
TMT-A		X		X	X
WMS-R-numbers forward		X		X	X
TMT-B		X		X	X
WMS-R-numbers backwards		X		X	X
RWT		X		X	X
Study period, Part B					
Time point	*t*_−2_		*t*_−1_	*t*_1_	*t*_2_
Enrollment					
Eligibility screen			X		
Informed consent			X		
Allocation			X		
Interventions					
Kidney transplantation	X				
Assessments					
ROCFT			X	X	X
VLMT			X	X	X
TMT-A			X	X	X
WMS-R-numbers forward			X	X	X
TMT-B			X	X	X
WMS-R-numbers backwards			X	X	X
RWT			X	X	X

Part A:

All included individuals undergo a detailed neurocognitive test battery on the day of transplantation (deceased kidney donation), or within 14 days before transplantation (living kidney donation). The neurocognitive test battery will be repeated after 3 and 12 months.

For individuals on the waiting list for deceased donor kidney transplantation we aspire to also carry out neurocognitive tests during standard visits to the hospital. Standard visits are typically several years apart and the date of transplantation is unforeseeable. Therefore, we expect not to be able to gather respective data for the majority of our participants and rather, will use it descriptively and for qualitative analyses.

Part B:

All included individuals who have already undergone transplantation and are in outpatient follow-up will undergo the same neurocognitive test battery as individuals in part A at baseline, after 3 months, and after 12 months.

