### Neuropsychological assessment

A battery of standardized cognitive tests will be performed at different timepoints (Table 1). Parallel test forms will be used at follow-up to account for learning effects. The order in which the parallel test forms are presented will be counterbalanced so that each parallel test form wil be administered with the same frequency at each test time point.

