#### The cognitive test battery

We first administer the Mini-Mental Status Examination (MMSE) [17] as a neurocognitive screening test, together with a test battery consisting of five tests, assessing the cognitive domains of selective attention, verbal and visual memory with short-delay and long-delay memory conditions, verbal working memory, word fluency and symbol processing. Raw scores are transformed into z-scores adjusted for age, and if available sex, as well as years of education.

The individual’s degree of impairment will be stratified using the algorithm adopted by Murray and colleagues [1] based on the Mayo criteria for mild cognitive impairment (MCI) [18] and the Diagnostic and Statistical Manual, fifth Edition, criteria for major neurocognitive impairment as approximate guidelines [19].

Individuals will be classified depending on their extent of impairment and the number of affected domains as.Unimpaired: performance better than 1.5 standard deviations (SD) below the norm sample in any test considered for the classification.Mildly impaired: mild deficits (scores 1.50 to 1.99 SD below the norm sample) in only one domain.moderately impaired: deficits in two domains or a severe deficit (2.0 SD below the norm Sample) in one domain.Severely impaired: deficits in at least two domains.

The domains of executive functions (semantic and phonemic fluency, working memory, and mental flexibility), verbal memory (immediate and delayed recall, recognition), visual memory (delayed recall), and attention (symbol processing speed) are considered in the classification.

For this purpose, we will use the following validated tests (Table 2):

**Table 2 Tab2:** The different neurocognitive tests and their affiliation to a particular cognitive domain

Cognitive domain	Test
Visual memory	ROCFT
Verbal memory	VLMT
Attention	TMT A WMS-R–numbers forward
Executive function	TMT B WMS-R–numbers backwards RWT

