### Sample size calculation

In order to investigate the prevalence of MCI or dementia, all individuals currently registered on the local transplant list, who are able to consent and agree to participate in the study, will be included. Currently, this list includes 142 individuals (75 individuals are in status T (transplantable), 67 individuals are in status NT (non-transplantable).

With regard to outcome measures, previous studies have shown highly significant improvements in some domains after transplantation [36], but have not reported effect sizes or statistical parameters that could be used to calculate effect sizes. Harciarek and colleagues [37, 38] report moderate to strong “time × comparison with healthy controls” interaction effects. We therefore conservatively expect to find low to medium effect sizes. For the detection of low to medium (*f* = 0.20) within-person effects with 3 measurement time points and 2 groups using a repeated-measures ANOVA as explained above, a power (1 – *β* (type II error probability) of 0.80 and a type-I error probability (*α*) of 0.05, a sample size of 42 is necessary [39, 40]. We therefore aim for a sample size of 50 persons for the follow-up measurements.

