### Primary outcome measure

The primary outcome measure will be cognitive performance. (a) We will compare cognitive performance before and after kidney transplantation, up to 12 months after transplantation in a population of patients who did not yet receive kidney grafts before enrollment in the study (part A) and (b) we will also investigate the development of cognitive performance over a period of 12 months in a population of patients who already received kidney grafts before enrollment in the study (part B).

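### Primary outcome (a) reads the before/after change in Part A as the effect of transplantation; the analysis names no Part A versus Part B contrast over time, so a retest gain can be credited to the graft

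*Protocol article*

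**What the plan says.** - **Claim.** The Methods part of the abstract names "the effect of kidney transplantation on the cognitive performance up to 12 months after transplantation" as primary outcome (a). The Background part of the abstract and the opening of the Discussion add the aim of finding out whether transplantation *per se* improves cognition.
- **Comparison for (a).** Primary outcome measure: "We will compare cognitive performance before and after kidney transplantation, up to 12 months after transplantation", in Part A patients only. Outcome (b) follows Part B separately over 12 months.
- **Model.** Statistical analysis: "This is a within-group design with three measurement time points", and "The time of measurement and other control variables listed above represent the independent variables". Group differences appear later, under exploratory questions, with a t-test or Mann-Whitney test.
- **Part B.** Inclusion and exclusion criteria: already transplanted patients "will undergo the same neurocognitive test battery as individuals in part A at baseline, after 3 months, and after 12 months".
- **Sample size.** Sample size calculation: 42 patients for a within-person effect of f = 0.20, with "3 measurement time points and 2 groups using a repeated-measures ANOVA as explained above". The groups are not named. The expected effect size is argued from published interactions of time with a healthy control group. The target is 50 persons for follow-up.
- **Safeguards.** Neuropsychological assessment: "Parallel test forms will be used at follow-up to account for learning effects", in counterbalanced order. The cognitive test battery: "Raw scores are transformed into z-scores adjusted for age, and if available sex, as well as years of education". Stress experience adds a rating of current stress before and after the pre-transplant testing, and Hair cortisol records steroid doses in all patients.

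**The concern.** A change from before to after transplantation in one group contains the transplant effect together with everything else that changes between visits. Here that includes growing familiarity with the tasks. It also includes recovery from a baseline that deceased-donor recipients take on the day of transplantation, a setting the Discussion itself concedes may be suboptimal.

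Parallel forms limit memory for specific items and balance form difficulty across visits, but they do not remove familiarity with the task format. Norms for age, sex and education do not adjust for repeated testing.

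Part B meets the same battery at the same intervals with no change in graft status during the study, so it is exposed to the same retesting. If its course is only described alongside Part A, that information is not used for the primary question. A significant Part A time effect could then be published as an effect of transplantation when some or all of it is retest gain.

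**Working it through.** **Inputs.** From the protocol: three visits, α = 0.05, power 0.80, f = 0.20, two groups, N = 42, target 50 for follow-up, 100 enrolled overall. Assumed, because the document gives none: correlation ρ between visits of 0.5 (0.7 as a variant), sphericity, scores in SD units, and a retest gain r of 0.1, 0.2 or 0.3 SD present at both follow-ups, so that visit means are (0, r, r). It is not stated whether the 50 are per part or in total, so Part A is taken as n = 50 or n = 25.

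**1. The plan's own figure.** λ = f² × N × 3/(1 − ρ) = 0.04 × 42 × 3/0.5 = 10.08, with df 2 and 2(42 − 2) = 80. Power is 0.803, so 42 is reproduced. With two groups and three visits, the time effect and the group-by-time interaction have the same λ and df, so 42 serves either test at f = 0.20.

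The same f means different things in the two tests. For the pattern (0, g, g):
- time effect: f = g√(2/9), so f = 0.20 is a gain of g = 0.42 SD;
- interaction: f = g/√18, so f = 0.20 is a difference in change of g = 0.85 SD.

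**2. Part A time effect when transplantation does nothing.** λ = n × (2/3)r²/(1 − ρ), df 2 and 2(n − 1). For n = 50, ρ = 0.5, r = 0.2: λ = 50 × 0.6667 × 0.04/0.5 = 2.67, giving 0.282.

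| Part A | r = 0.1 | r = 0.2 | r = 0.3 |
|---|---|---|---|
| n = 50, ρ = 0.5 | 10% | 28% | 57% |
| n = 50, ρ = 0.7 | 14% | 44% | 80% |
| n = 25, ρ = 0.5 | 7% | 16% | 30% |

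These are for one outcome at 0.05, before the false discovery rate correction.

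**3. The part-by-time test under the same conditions.** If both parts gain equally, simulation gives 4.6 to 5.2%, which is the nominal level. If Part B gains half as much as Part A (50 per part, ρ = 0.5), it gives 6%, 8% and 11%.

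**4. What the contrast does not remove.** Suppose the Part A baseline alone is depressed by 0.3 SD on average (an assumption). The difference in change is then 0.3 SD with no transplant effect. λ = (50/2) × (2/3) × 0.09/0.5 = 3.0, df 2 and 196, and the interaction is significant in about 32% of cases.

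**5. Precision.** The SD of change is √(2(1 − ρ)) = 1 at ρ = 0.5. The 95% CI half-width for baseline-to-month-12 change is 0.284 in Part A alone (n = 50) and 0.397 for A minus B (50 per part), a ratio of 1.40. The difference detectable with 80% power is 0.40 against 0.57 SD; with 25 per part it is 0.58 against 0.81 SD.

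Interaction power (ρ = 0.5, same λ as in step 4 with the true difference in place of 0.3):

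| True difference in change | 0.4 SD | 0.5 SD | 0.6 SD |
|---|---|---|---|
| 50 per part | 53% | 73% | 88% |
| 25 per part | 28% | 42% | 57% |

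**The case against.** **A part-by-time test may be intended.** A reader might infer that none is planned. The document does not support so firm a statement. The sample size section describes the ANOVA as a two-group one, Levene's test presupposes groups, the model includes the influence of further predictors, and a fuller analysis plan may exist. The two groups could also be living and deceased donor recipients. What stands is that the text calls the design within-group, confines (a) to Part A, and names neither study part nor its interaction with time.

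**The sample size is wrong.** A reader might infer this too. It is not: 42 is reproduced and serves both tests at f = 0.20.

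**The hazard is exaggerated.** The gains and correlations are assumptions, and the counterbalanced parallel forms should keep gains small. It would be too strong to say that a false transplant effect would often be reported: that needs the upper end of the range. The error correction lowers the rates somewhat, but it guards against chance findings, not against misattributing a real change.

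**Other influences are measured.** This is fair. Acute stress, steroid doses and medication are recorded and may enter as control variables. None of them captures retest gain.

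**The steroid taper is part of the treatment.** This is also fair. A reader might count the taper as a confounder of (a), but an effect of transplantation with its regimen is a legitimate target. Only *per se* strains against it, and the document gives neither size nor direction for any steroid effect on cognition.

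**Part B is a poor control.** It is not randomised, is already grafted, and has no fixed time since transplantation. A reader might infer that the interaction would isolate the transplant effect. It would not, as step 4 of the working shows, so it should not be the sole basis for a causal claim.

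**Conclusion.** The concern holds as a mismatch between the stated claim and the stated analysis. The Part A time effect validly describes change after transplantation with its regimen; it does not support an effect of transplantation *per se*. With no transplant effect, an assumed retest gain of 0.1 to 0.3 SD makes it significant in 10 to 57% of cases with 50 patients, or 7 to 30% with 25, at correlation 0.5. The lower end is more plausible given the parallel forms.

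The part-by-time contrast holds the nominal 5% only if both parts share the retest gain and nothing else distorts Part A alone. It is therefore a worthwhile supportive analysis from data already being collected, not proof of causation. The change should be made; without it the study remains sound as a description.

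**What to change.** 1. Keep the Part A time effect, reported as change after transplantation with its regimen, and keep the Part B course as a description.
2. Add study part (A or B) and part-by-time to the repeated-measures ANOVA as a prespecified supportive contrast. Report the A minus B difference in baseline-to-month-12 change with its 95% CI. Say which two groups the sample size section means.
3. Delete *per se* in the Abstract and Discussion. Claim nothing beyond change after transplantation unless the contrast supports it.
4. Even then, state in the limitations that the contrast removes only shared retest gain. It does not remove non-random differences between the parts, the day-of-transplant baseline or the steroid course. As a check on the baseline, use the acute-stress item and compare change between living and deceased donor recipients.

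**Cost.** No new patients, visits or treatment. The contrast has a CI about 1.4 times as wide as Part A alone and, with 25 per part, only 57% power even for a 0.6 SD difference. The report should therefore say that a non-significant contrast does not show absence of an effect.
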